To test the degree to which change in reward sensitivity mediates the 12 weeks response to pramipexole of both depressive, and specifically anhedonic, symptoms	Change in QIDS-SR_16_ and SHAPS scores between baseline and week 12 and change in reward sensitivity between baseline and week 2	Baseline, week 2, week 12
To compare the extent to which an increase in reward sensitivity predicts therapeutic response	Change scores in the learning/decision making task at 2 weeks and the change in the QID-SR_16_ at 12 weeks	Week 2, week 12
To explore the extent to which reward sensitivity at baseline predicts therapeutic response	Baseline scores on the learning/decision making task and the change in QIDS-SR_16_ at 12 weeks	Baseline, week 12
To explore the extent to which level of anhedonia at baseline predicts therapeutic response	Baseline scores on SHAPS and change in the QIDS-SR_16_ at 12 weeks	Baseline, week 12
To compare the effect of pramipexole and placebo on the trajectory of symptoms of depression	QIDS-SR_16_ scores collected weekly across 48 weeks of the trial	Weekly for week 1–48
To compare the effect of pramipexole and placebo on response and remission rates, using the QIDS-SR_16_ at twelve weeks	QIDS-SR_16_ response, defined as a reduction of <50% of baseline scores at week 12, remission as a score of <5 at week 12	Baseline, week 12
To compare the impact of pramipexole and placebo on symptoms of anhedonia, anxiety and clinician rated depression	Change scores for the SHAPS, GAD-7 and QIDS-C between baseline and week 12	Baseline, week 12
To compare the impact of pramipexole and placebo on functional outcome over the 48 weeks of treatment	Change scores for the WSAS-screener between baseline and week 48	Baseline, weeks 12, 24, 36 and 48
To determine the impact on quality of life and capability well-being of pramipexole relative to placebo over 48 weeks	Change in the following over 48 weeks: EQ-5D-5L ICECAP-A OxCAP-MH	Baseline, weeks 12, 24, 36 and 48
To examine the health/social care and broader societal costs of patients relative to placebo over 48 weeks	Change in the following over 48 weeks: HEQ	Baseline, weeks 12, 24, 36 and 48

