#### Assignment of intervention

Each participant will be randomised at a ratio of 1:1 to either pramipexole or a matched placebo. A non-deterministic algorithm will be used to produce treatment groups balanced for important prognostic factors by minimising separately on four variables including (1) trial site, (2) age (18–50, vs >50), (3) gender (M/F) and (4) baseline quick inventory of depressive symptomatology self-report 16 (QIDS-SR16) severity (11–15 vs 16–20 vs >20).

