### Statistical methods

The primary outcome (change in QIDS-SR16 between baseline and week 12) will be analysed using a generalised linear mixed model utilising data collected at each weekly time point from randomisation and including the baseline outcome and minimisation factors as fixed effects. The model will include a random intercept for each participant to account for the repeated measures on the same participant and an interaction term for the treatment by time interaction to allow the treatment effect to differ at each time point.

Continuous secondary outcomes will be analysed using generalised linear models. The dichotomous secondary outcomes will be analysed using a logistic mixed effects regression model. These analyses will include a fixed effects randomised group and baseline level of the QIDS-SR_16_, with participants and trial site accounted for as random effects. Minimisation variables will be included as explanatory factors in the models. Mediational analysis will test whether changes in reward sensitivity mediate the effect of pramipexole on depressive symptoms. Health economic data analysis will assess group differences in quality of life, well-being, and work performance using a cost-utility analysis.

The primary and efficacy-based secondary analyses will be performed using an intention-to-treat approach for all randomised participants. Analyses of the mechanistic secondary outcomes and health economic outcomes will be performed in the set of participants who have the data required for the specific analyses (ie, no imputation will be performed for these analyses). Acceptability analyses will be performed on a subgroup of participants and trial clinicians who provide separate consent for aspect of the trial.

The main health economic analysis will include: (1) a detailed patient-level cost analysis of health, social care and other broader societal costs for both the pramipexole and placebo arms of the trial and (2) an incremental within-trial economic evaluation comparing the pramipexole and placebo arms of the trial in terms of their costs and outcomes over the 48-week trial follow-up period.

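### The logistic model for week-12 response and remission carries a participant random effect that one binary value per person cannot support, and it appears to enter trial site twice

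*Protocol article*

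**What the plan says.** Table 1 of the protocol article gives the objective as "To compare the effect of pramipexole and placebo on response and remission rates, using the QIDS-SR_16_ at twelve weeks". It defines "response, defined as a reduction of <50% of baseline scores at week 12, remission as a score of <5 at week 12", and lists baseline and week 12 as the only time points. (The direction of the inequality for response is a separate matter and plays no part here.) Each participant therefore has one response value and one remission value.

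Statistical methods states: "The dichotomous secondary outcomes will be analysed using a logistic mixed effects regression model". The next sentences cover the continuous and dichotomous secondary outcomes together. They name randomised group and baseline QIDS-SR16 as fixed effects, and continue "with participants and trial site accounted for as random effects. Minimisation variables will be included as explanatory factors in the models". Assignment of intervention describes the allocation as "minimising separately on four variables including (1) trial site", followed by age, gender and baseline severity.

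The primary model in the same section is different. It uses every weekly value, explains the participant intercept by the repeated measures, and includes a treatment-by-time interaction. None of this is stated for the dichotomous outcomes.

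**The concern.** A participant random intercept describes correlation among several observations on the same person. With a single binary observation per person there is no such correlation to observe. The intercept variance then acts almost purely as a scale factor on all the coefficients: a larger variance with proportionally larger log odds ratios fits the data about equally well. The software may return zero variance, a convergence warning, or an arbitrary positive variance, and the odds ratio moves with it. Response and remission odds ratios are readily quoted and pooled, so a figure whose size depends on where an optimiser stopped would be a poor result to publish.

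The second issue is site. It is listed among the random effects. It is also one of the minimisation variables, all of which are to be explanatory factors, with no exception made for site. Read literally, site enters the same model twice.

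**Working it through.** **Inputs.** From the protocol article: one binary per participant at week 12 (Table 1); participant and site random effects (Statistical methods); site as a minimisation variable and 1:1 allocation (Assignment of intervention); five named sites, one pilot plus four (Recruitment); a 3-point difference, SD 5.4, 90% power and 20% loss (Sample size). The article gives no figure for the logistic model itself. The sample size is used here only to set N.

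**1. Sample size reproduced (two-sided alpha assumed).** n per group = 2 × [5.4 × (z for alpha + z for power) / 3]².
- Alpha 0.05: 68.09, against 68 stated; 136 / 0.8 = 170.
- Alpha 0.025: 80.42, rounded up to 81; 81 / 0.8 = 101.25, rounded up to 102 per group, 204 in total.

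The stated figures reproduce. The check below therefore uses N = 162 (2 × 81) and N = 204.

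**2. Illustrative size of the scaling.** The usual approximation is: conditional log OR ≈ marginal log OR × √(1 + 0.346 × SD²). The Introduction quotes response rates of 40% and 27% from an earlier trial of 65 patients; they serve only as an example.
- Marginal OR = (0.40/0.60) / (0.27/0.73) = 1.80; log OR = 0.589.
- SD 1: 0.589 × √1.346 = 0.683, OR 1.98.
- SD 2: 0.589 × √2.384 = 0.909, OR 2.48.

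**3. Can the data choose the SD?** Single-binary data were simulated with five sites, baseline score, age band, gender, a treatment log OR of 0.6 and a true participant SD of 1.5 (all assumed). The model was fitted with the participant SD held at each value in turn. One data set at N = 162 gave:

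| Participant SD | Log-likelihood | Treatment log OR | z | OR |
|---|---|---|---|---|
| 0 | −105.839 | 0.597 | 1.76 | 1.82 |
| 1 | −105.839 | 0.716 | 1.82 | 2.05 |
| 2 | −105.840 | 0.971 | 1.78 | 2.64 |
| 3 | −105.840 | 1.278 | 1.80 | 3.59 |
| 4 | −105.841 | 1.607 | 1.80 | 4.99 |

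The log-likelihood changes by 0.002 while the OR goes from 1.82 to 4.99. The z value stays near 1.8.

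Over 60 simulated trials at N = 204, with SD values of 0, 1, 2 and 3, the log-likelihood range had a median of 0.03 and a maximum of 0.18. The best-fitting SD was 0 in 27 trials and 3 in 30, so it lay at an end of the grid in 57 of 60. The median OR moved from 1.57 at SD 0 to 2.60 at SD 3, and the median z from 1.47 to 1.49.

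**4. Contrast with repeated binaries.** With 12 binary values per participant (N = 204, same true SD), the log-likelihood peaks clearly at SD 1.5: −1417.1, against −1608.1 at SD 0. The difficulty comes from having one row per person, not from the model class.

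**5. Site as both fixed and random.** In a simulated data set of N = 204 with five sites, the log-likelihood is highest at site SD 0 (−122.29) and falls to −127.81 at SD 1. The treatment log OR moves only from 0.359 to 0.367. The random site term collapses to zero and the treatment estimate is scarcely touched.

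**The case against.** The strongest reply is that the article does not limit the logistic model to week-12 rows. The sentence on random effects covers all secondary outcomes, some of them collected repeatedly. The primary outcome is also defined as a change to week 12, yet its model uses all weekly data. QIDS-SR16 is collected weekly to week 12, so response and remission could be modelled repeatedly, and step 4 shows that the participant variance is then well estimated. This stands as a possibility. Against it, Table 1 gives weeks 1 to 12 for the primary outcome but only baseline and week 12 here, and no time or treatment-by-time term is stated. A repeated-binary model without that interaction would give one treatment effect common to all weeks, not the week-12 comparison in the objective. Neither reading works as written.

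On site, "Minimisation variables will be included as explanatory factors in the models" follows directly after site has been made a random effect, and it does not say fixed. The authors may have meant site as random and the other three variables as covariates. That is a fair reading, and one clause would settle it.

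A reader might also infer more than the document supports:
- That the model is formally not identified. With covariates, the logistic-normal form gives weak formal identification; the failure is practical.
- That the result would not depend on the data. The z value is essentially unchanged across participant SDs, so direction and test remain driven by the data. If the variance collapses to zero, the fit is ordinary logistic regression in respect of the participant term.
- That the double entry of site makes the treatment effect inestimable. Step 5 shows that it does not.
- That termination of treatment for intolerance has the same defect. The article does not expressly assign that outcome to this model.

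**Conclusion.** The point holds as an inconsistent specification of a secondary analysis. Taken with the week-12 definitions in Table 1, the stated model has a participant variance that cannot be estimated in practice, so the size of the conditional odds ratio is arbitrary while its test is not. The illustrative range is 1.80 to about 2.0 or 2.5 at assumed participant SDs of 1 and 2. It rests on response rates from another trial and does not predict this trial's result. The simulation results depend on the assumed site number, effects and true SD, but the flat likelihood follows from having one binary per person. The treatment of site is a redundancy and an inconsistency, with no material effect on the treatment estimate. The primary analysis and the sample size are unaffected.

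**What to change.** State which rows the logistic model uses, and match the terms to them:
- **Week-12 response and remission:** drop the participant random effect. Fit a logistic regression on arm, baseline QIDS-SR16 and the minimisation factors, with site entered once, as fixed or as random.
- **If repeated binaries are intended:** keep the participant random effect, add time and treatment-by-time terms, enter site once, and name the week-12 contrast as the reported result.

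The cost is a few words in the protocol or the analysis plan. No data collection, sample size or primary analysis changes.

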#### EQ-5D-5L

This is a standardised measure of health status and provides a generic measure of health-related quality of life for clinical and economic appraisal (https://euroqol.org/eq-5d-instruments/eq-5d-5l-about/). The scale has five dimensions (mobility, self-care, usual activities, pain/discomfort and anxiety/depression) and five levels for each dimension (no problems, slight problems, moderate problems, severe problems, extreme problems. A visual scale records the respondent’s self-rated health with endpoints labelled ‘the best health you can imagine’ and ‘the worst health you can imagine’. Participants will complete EQ-5D-5L on True Colours at week 0, 12, 24, 36 and 48.

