#### Oxford CAPabilities questionnaire-Mental Health

This is a validated mental health specific capability well-being scale with 16 items.^28^ The items cover different domains of well-being (overall health, social and recreational activities, loss of sleep due to worry, friendship and support, having suitable accommodation, feeling safe, likelihood of discrimination and assault, freedom of personal and artistic expression, appreciation of nature, self-determination, and access to activities or employment), each scored on a 5-point Likert scale. Participants will complete Oxford CAPabilities questionnaire-Mental Health (OxCAP-MH) on True Colours at week 0, 12, 24, 36 and 48.

Health Economics Questionnaire (HEQ). The HEQ has specifically been developed for mental health economic evaluations and is now also complemented with a COVID-19-related module (https://zenodo.org/record/4559752). It measures health and social care resource use, medication, absenteeism from work and presenteeism as well as sociodemographic background information. Participants will complete this on True Colours at week 0, 12, 24, 36 and 48.

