The primary health economic analysis will be a cost-utility analysis from a health and social care perspective where quality-adjusted life-years will be calculated using utility values from the EQ- 5D-5L. Secondary economic analyses using the ICECAP-A and the OxCAP-MH capability indices as outcome measures will be also carried out. Further analyses will estimate cost-effectiveness from a societal perspective. All economic analyses will be on an intention-to-treat basis.

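### The economic outcomes are limited to participants with data and no imputation, yet all economic analyses are called intention-to-treat; the two statements must be reconciled

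*Protocol article*

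**What the plan says.** Three statements in Statistical methods bear on who enters the economic analysis.

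- On efficacy: "The primary and efficacy-based secondary analyses will be performed using an intention-to-treat approach for all randomised participants".
- On the mechanistic and economic outcomes, the next sentence confines the analysis set to those who "have the data required for the specific analyses (ie, no imputation will be performed for these analyses".
- On the economic analyses, at the end of the section: "All economic analyses will be on an intention-to-treat basis".

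The economic evaluation compares the arms "in terms of their costs and outcomes over the 48-week trial follow-up period". Its primary analysis is a cost-utility analysis from a health and social care perspective, in which "quality-adjusted life-years will be calculated using utility values from the EQ- 5D-5L".

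The EQ-5D-5L section gives the utility schedule: "Participants will complete EQ-5D-5L on True Colours at week 0, 12, 24, 36 and 48". The HEQ, which supplies resource use and work loss, is described under the Oxford CAPabilities questionnaire heading and has the same schedule: "Participants will complete this on True Colours at week 0, 12, 24, 36 and 48".

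The only loss figure is the 20% allowance under Sample size, in a calculation built on the week-12 difference. No figure is given for loss or questionnaire completion at 48 weeks.

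**The concern.** The article fixes a missing-data rule and then names a population that the rule cannot deliver. This is a conflict between two stated rules, so it is not a detail left to the analysis plan. A health economist working from the article could defend either base case, including after seeing the data.

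The choice matters more here than for a single-visit outcome. A QALY over 48 weeks is normally an area under the utility curve, and a cost total is a sum over all recall periods, so each needs the full series. If nothing is imputed, a participant who misses one wave normally contributes nothing, and the waves that were observed are discarded. The primary outcome, by contrast, is analysed with a mixed model on weekly data, which tolerates gaps.

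If missing a wave is related to tolerability or lack of benefit, and differs by arm, the complete cases are no longer comparable randomised groups. The incremental cost per QALY would then describe a subset, although it would be reported as intention-to-treat. The allowance for loss in the sample size protects precision; it does not protect against this.

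**Working it through.** **Step 1. Reproduce the plan's own figure.** Inputs from Sample size: difference 3, SD 5.4 (3/5.4 = 0.556, given as 0.56), power 90%, alpha 0.05 or 0.025 (taken as two-sided), loss 20%. Allocation is 1:1 (Assignment of intervention). The formula is n per group = 2 × (z for alpha + z for power)² / d².

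- Alpha 0.05: 69 per group with d = 3/5.4, and 68 with d = 0.56. The plan has 68. Inflated: 68/0.8 = 85 per group, 170 in total, as stated.
- Alpha 0.025: 81 per group with d = 3/5.4. The plan has 81. Inflated: 81/0.8 = 101.25, rounded up to 102 per group, 204 in total, as stated.

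The sample size reproduces, so 204 is the number randomised in what follows.

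**Step 2. Set the populations side by side.**

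| Statement | Population | Missing data |
|---|---|---|
| Efficacy analyses | all randomised, called intention-to-treat | mixed model for the primary outcome |
| Economic outcomes | those with the required data | no imputation |
| All economic analyses | intention-to-treat | not mentioned |

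Under the first row's meaning of intention-to-treat, the second and third rows agree only if nobody has missing economic data.

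**Step 3. How large might the subset be?** The documents do not give this, so it is a range under stated assumptions. Baseline is taken as complete, leaving four post-baseline waves (weeks 12, 24, 36 and 48). EQ-5D-5L and HEQ are taken to be missed together, since they share schedule and platform.

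- If the same people are missing at every wave and 20% is the total loss: 204 × (1 − 0.20) = 163.2, about 163 (80%).
- If each wave is missed independently with probability m, complete cases = 204 × (1 − m)⁴:

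| m per wave | (1 − m)⁴ | Complete of 204 |
|---|---|---|
| 10% | 0.656 | about 134 |
| 15% | 0.522 | about 106 |
| 20% | 0.410 | about 84 |

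A fresh 20% loss in each 12-week interval gives the same last row, since 0.8⁴ = 0.41.

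**Step 4. When would fewer than half remain?** Solve (1 − m)⁴ = 0.5: m = 1 − 0.5^(1/4) = 0.159. Independent missingness has to exceed about 16% per wave. The article gives no such rate.

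**The case against.** The strongest reply is that intention-to-treat in the economic sentence may mean only that participants are analysed in the arm to which they were randomised, whatever their adherence. The efficacy sentence adds that all randomised participants are included; the economic sentence does not. On that reading an available-case set and intention-to-treat can coexist. This softens the conflict but does not remove it: the reader still cannot tell which population is meant, and the no-imputation rule stands.

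Secondly, the set is defined by the data each analysis requires, so it need not mean all five waves every time; EQ-5D-5L at one time point would need less. Nor does ruling out imputation exclude a likelihood-based repeated-measures model, which keeps partial records. Both points stand. They are why the loss of participants with a missed wave is described as the normal consequence for cumulative totals and not as something the article says.

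Thirdly, stopping medication is not the same as stopping questionnaires. Telephone contact is planned every four weeks to week 48, and ending treatment for intolerance is itself an outcome. The Introduction reports heavy dropout in an earlier study at a higher dose and few completers in a small combination arm, but neither gives a rate for this trial. Selection is therefore a risk, not a demonstrated effect.

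A reader might also infer three stronger claims that the documents do not support.

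- **That the economic result would rest on a minority.** This needs more than about 16% independent missingness per wave, or 20% fresh loss in every 12-week interval. The only stated loss figure, taken as the total, leaves about 80%.
- **That the standard error would be about 1.6 times larger.** The ratio √(204/84) = 1.56 sets the worst assumption against 204 fully observed participants. The plan never expected that many, and imputation would not recover it.
- **That the same rule damages the reward-sensitivity comparison.** The final intention-to-treat sentence covers economic analyses only, and a mixed model on available task data needs no imputation, so it is compatible with the text as written.

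**Conclusion.** The point holds as an inconsistency with a practical consequence. Within one section the article rules out imputation and limits the economic outcomes to participants with data, and then calls all economic analyses intention-to-treat, a term it has used for all randomised participants. For 48-week totals built from five questionnaire waves, the restrictive rule would normally leave a possibly selected subset.

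The size is not fixed by the documents. Under the assumptions shown, it runs from about 163 of 204 (80%) to about 84 of 204 (41%), and the direction of any bias is unknown. The need to reconcile the statements does not depend on where in that range the trial falls.

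The economic evaluation is a secondary objective and the primary QIDS-SR16 analysis is untouched. The correction should be made before the economic data are analysed, but it does not threaten the trial's main conclusion.

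**What to change.** Remove the no-imputation rule for the economic outcomes and state one base case:

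- **Population:** all randomised participants, analysed as allocated.
- **Missing data:** multiple imputation, by arm, of missing EQ-5D-5L utilities and HEQ costs, using baseline utility, the minimisation factors and observed QIDS-SR16 scores.
- **Sensitivity analyses:** complete cases, and missing-not-at-random scenarios that shift the imputed values.

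Say in one sentence what intention-to-treat means for the economic analyses, so that the two statements in Statistical methods agree. The rule for the mechanistic outcomes can stay as it is.

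The cost is wording in the health-economics analysis plan and modest extra programming. No visit, sample size or treatment changes. The downside is that the base case then relies on data being missing at random. That cannot be verified, and the sensitivity analyses are there to show how far the result depends on it.
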